# Study protocol: Effects of active versus passive recharge burst spinal cord stimulation on pain experience in persistent spinal pain syndrome type 2: a multicentre randomized trial (BURST-RAP study)

**DOI:** 10.1186/s13063-022-06637-7

**Published:** 2022-09-05

**Keywords:** Neuromodulation, Burst SCS, Spinal cord stimulation, Persistent spinal pain syndrome type 2, Pain relief, Motivational-emotional aspects of pain

## Abstract

**Background:**

Spinal cord stimulation (SCS) has shown to be an effective treatment for patients with persistent spinal pain syndrome type 2 (PSPS Type 2). The method used to deliver electrical charge in SCS is important. One such method is burst stimulation. Within burst stimulation, a recharge pattern is used to prevent buildup of charge in stimulated tissues. Two variations of burst waveforms are currently in use: one that employs active recharge and one that uses passive recharge. It has been suggested that differences exist between active and passive recharge paradigms related to both efficacy of pain relief and their underlying mechanism of action. Active recharge has been shown to activate both the medial spinal pathway, engaging cortical sensorimotor areas involved in location and intensity of pain, and lateral pathway, reaching brain areas involved with cognitive-emotional aspects of pain. Passive recharge has been suggested to act via modulation of thalamic neurons, which fire in a similar electrical pattern, and thereby modulate activity in various cortical areas including those related to motivational and emotional aspects of pain. The objective of this randomized clinical trial is to assess and compare the effect of active versus passive recharge Burst SCS on a wide spectrum of pain in PSPS Type 2 patients.

**Methods:**

This multicentre randomized clinical trial will take place in 6 Dutch hospitals. PSPS Type 2 patients (*n=94*) will be randomized into a group receiving either active or passive recharge burst. Following a successful trial period, patients are permanently implanted. Patients complete the Pain Catastrophizing Scale (PCS) (primary outcome at 6 months), Numeric Pain Rating Scale (NRS), Patient Vigilance and Awareness Questionnaire (PVAQ), Hospital Anxiety and Depression Scale (HADS), Quality of Life (EQ-5D), Oswestery Disability Index (ODI), Patient Global Impression of Change (PGIC) and painDETECT questionnaires (secondary outcomes) at baseline, after trial, 1, 3, 6 and 12 months following implantation.

**Discussion:**

The BURST-RAP trial protocol will shed light on possible clinical differences and effectivity of pain relief, including emotional-motivational aspects between active and passive burst SCS in PSPS Type 2 patients.

**Trial registration:**

ClinicalTrials.gov registration: NCT05421273. Registered on 16 June 2022. Netherlands Trial Register NL9194. Registered on 23 January 2021.

## Administrative information

**Table Taba:** 

Data category	Information
Primary registry and trial identifying number	Clinicaltrials.gov: NCT05421273, registered Netherlands Trial Register NL9194, registered
Date of registration in primary registry	23 January 2021
Secondary identifying numbers	n/a
Source(s) of monetary or material support	Abbott Laboratories
Primary sponsor	Abbott Laboratories
Secondary sponsor(s)	N/A
Contact for public queries	[name] [contact], [name] [contact]
Contact for scientific queries	[name] [contact], [name] [contact]
Public title	N/A
Scientific title	Effects of Active Versus Passive Recharge Burst Spinal Cord Stimulation on Pain Experience in Persistent Spinal Pain Syndrome Type 2: A Multicenter Randomized Trial (BURST-RAP study)
Countries of recruitment	The Netherlands
Health condition(s) or problem(s) studied	Persistent Spinal Pain Syndrome Type 2
Intervention(s)	Passive recharge burst (Burst DR^TM^) spinal cord stimulation
	Active recharge burst spinal cord stimulation
Key inclusion and exclusion criteria	Ages eligible for study: ≥18 years Sexes eligible for study: both
	Inclusion criteria Subjects between 18 and 65 years of age At least moderate level of catastrophizing as measured with the Pain catastrophizing scale (PCS) of at least 20. History consistent with PSPS Type 2 of at least 6 months
	Exclusion criteria Subject is unable to operate the device Severe spinal column degeneration likely to cause technical problems with neuromodulation, to be assessed by the treating physician
Study type	Investigator initiated multicenter randomized clinical trial
	Allocation: Unblinded randomization
	Primary purpose: Pain Experience
Date of first enrolment	February 2022
Target sample size	94
Recruitment status	Recruiting
Primary outcome(s)	Change on the PCS scale
Key secondary outcomes	Change in low back and leg pain intenstity, PVAQ, HADS, EQ-5D, ODI, PGIC, analgesia intake and PainDETECT rates

## Background

Spinal cord stimulation (SCS) is increasingly being used for the treatment of patients with intractable chronic pain that are resistant to conventional treatment options [1]. SCS has been shown to reduce pain in patients with intractable chronic pain, improve quality of life and reduce use of analgesics, while maintaining a low rate of adverse effects [2]. The most common indication for spinal cord stimulation is persistent spinal pain syndrome type 2 (PSPS Type 2), previously referred to as failed back surgery syndrome (FBSS) [3–9]. PSPS Type 2 is marked by radicular neuropathic or neuroplastic leg or arm pain, sometimes combined with low back pain (LBP), resulting in a significant decline in their quality of life, psychological outlook and work productivity [3, 10–16].

Patients receiving conventional SCS, characterized by electrical pulses delivered in the 40–60Hz stimulation frequency range, experience paresthesia or a tingling sensations in the painful area. Burst SCS is a new stimulation paradigm that has been suggested to be even more effective compared to conventional SCS and is now approved worldwide [17]. Furthermore, burst SCS eliminates or greatly reduces the incidence of paresthesia [18], hinting at a different underlying mechanism of action as compared to conventional SCS [19]. Burst SCS consist of delivering groups of electrical pulses (also referred to as “burst trains”) which are repeated at a burst rate; within each burst train, several pulses are issued at an intra-burst rate [20]. Following each pulse a recharge pattern is required to prevent the buildup of charge in the stimulated tissue. Individual pulses are characterized by a pulse amplitude and pulse width.

Currently, two variations of burst-SCS are used in treatment of patients with intractable chronic pain. These two variations differ with respect to the recharge pattern employed in the burst train: on the one hand a burst paradigm employing passive recharge (referred to as BurstDR, developed by Abbott Laboratories [20, 21]) and on the other hand using an active recharge pattern (used by Boston Scientific [22–24]).

## Materials and methods

This multicentre randomized clinical trial will be undertaken in various Dutch Hospitals including the Rijnstate Hospital (Arnhem), Bravis Hospital (Roosendaal), Elizabeth TweeSteden Hospital (Tilburg), Diakonessen Hospital (Utrecht), Alrijne Hospital (Leiden) and the Amsterdam University Medical Hospitals (A-UMC). This protocol has been designed following Standard Protocol Items: Recommendations for Interventional Trials (SPIRIT) reporting guidelines [39].

### Patient population

Subjects are selected based on inclusion and exclusion criteria as displayed below. In order to detect changes in emotional state, patients must show at least a moderate level of pain catastrophizing (PCS ≥ 20) as based on research including catastrophizing PSPS Type 2 patients [4].

### Inclusion criteria

Subjects between 18 and 70 years of age.At least moderate level of catastrophizing as measured with the Pain Catastrophizing Scale (PCS) of at least 20 at first visit of the pain clinic.Chronic pain diagnosed as PSPS Type 2 for at least 6 months.Neurologic exam without marked motor deficit.LBP and/or leg pain intensity should be 5 or higher measured with the 11-box NRS 0-10.Meets all the inclusion criteria for the implantation of a neurostimulation system as typically utilized in the study centre. Depression is not an exclusion criteria.Subject has been screened by a multi-disciplinary panel including a psychologist and deemed suitable for implantation.Subject is able and willing to comply with the follow-up schedule and protocol.Subject is able to provide written informed consent.

### Exclusion criteria

Female subject of childbearing potential is pregnant/nursing or plans to become pregnant during the course of the study.Escalating or changing pain condition within the past month as evidenced by investigator examination.BMI ≥ 35.Subject has had injection therapy or radiofrequency treatment for their LBP or leg pain within the past 3 months.Subject currently has an active implantable device including ICD, pacemaker, spinal cord stimulator, or intrathecal drug pump.Subject is unable to operate the device.Severe spinal column degeneration likely to cause technical problems with neuromodulation, to be assessed by the treating physician.Previous neurostimulation therapy.

### Recruitment and consent

Subjects will be recruited from the site’s existing patient population and through new patient contacts through standard clinical practice. Patients will be asked to participate by their physician and presented with the patient information and informed consent form. Patients are given at least a week to consider their decision. At all times, subject are able to contact the research team or an independent specialist with questions. Patients are able to withdraw from the study at any time and without giving a reason to do so.

### Study procedure

 Following inclusion and consent, patients are randomized into two groups: passive burst SCS or active burst SCS. Randomization is performed by local study staff using Castor study management software. Patients are stratified per group and per center for PCS rate (two groups of 20-35 and 35-52), gender and pain location.

Procedures in this study do not deviate from standard neuromodulation care for PSPS Type 2 patients. First, a trial period occurs where patients are implanted with either two Abbott Octrodes or two Boston Scientific Infinion leads in the dorsalepidural space; during the procedure paresthesia testing is performed to achieve maximum overlap with the pain area of the patient. During this trial period, patients are stimulated by an external pulse generator. Stimulation settings are set by clinical programmers provided by Abbott and Boston Scientific, who individually assess optimal burst stimulation parameters for every individual participating patient. Due to the subsequent nature of the study, patients cannot be blinded. Following a test phase of 2 weeks and a minimal pain reduction of 50%, patients are implanted with an internal IPG (Proclaim 5/XR (Abbott Laboratories) or Waverwriter Alpha (Boston Scientific)). When pain reduction is less than 50%, the trial is expanded by 1 week, and other (non-burst) waveforms possible with the implanted system can be tried, with the aim to induce pain relief. These patients, with at least 50% pain relief, will remain in the study and complete long-term follow up questionnaires.

Data regarding pain state and mental attitude towards pain are collected at baseline, after trial, 1 month, 3 months, 6 months and 12 months following implantation. Patients will electronically complete the Pain Catastrophizing Scale (PCS) [38], Numeric Pain Rating Scale (NRS), Patient Vigilance and Awareness Questionnaire (PVAQ) [40, 41], Hospital Anxiety and Depression Scale (HADS) [42, 43], Quality of Life (EQ-5D) [44–46], Oswestery Disability Index (ODI) [47], Patient Global Impression of Change (PGIC) [48] and painDETECT [49, 50] questionnaires using the CASTOR data collection system. Additionally, use of pain medication alongside neuromodulation is recorded at every follow-up contact, as well as the mean charge per second (CpS) and mean charge per hour (CpH) as used by the stimulation apparatus in order to gain insight into electrical consumption.

Six months post implantation, the trial enters an open-label phase, running until 12 months. During this open-label phase, patients can switch to other non-burst waveforms permitted by the SCS system implanted with the aim to further increase pain relief. If, during any of the trial phases including the initial trial, patients encounter decreased efficacy or insufficient pain relief, they may enter the open label phase prematurely. A flow chart outlining study procedures is displayed in Fig. 1 and in Table 1.

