### Sample size calculation

This study follows a non-inferiority setup based on the primary outcome measure, the PCS. The non-inferiority limit of 7 points on the PCS scale (13.46%) was defined based on an estimation of the clinically meaningful score of PCS scores established on experience with this test at the main research centre. Previous literature investigating the clinically meaningful difference of the PCS scale estimates that this lies at around 44% [51]. However, as this study was performed in patients with subacute pain after whiplash injury, the decision was made to lower the non-inferiority limit for patients with PSPS Type 2, a chronic debilitating condition with neuropathic components.

In order to calculate group size, an estimation of the expected standard deviation (SD) was based on previous literature for FBSS patients with neuromodulation to be 12.04 points on the PCS scale [4]. In combination with a non-inferiority limit of 7 points, 80% power and 5% significance level, this results in a group size of 37 patients per group or 74 patients total. Compensating for a drop-out rate of 20% (including failed initial trials), we arrive at 92.5 patients. However, this is rounded to 94 patients in order to ensure even group size of 47 patients per group.

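### The two PCS randomisation strata both contain 35, and if all factors are crossed with blocking inside each cell, 48 to 72 cells for 94 patients give weak balance on PCS

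*Protocol article*

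**What the plan says.** Study procedure sets the strata: "Patients are stratified per group and per center for PCS rate (two groups of 20-35 and 35-52), gender and pain location". It also says who randomises: "Randomization is performed by local study staff using Castor study management software". It names no block size and no minimisation algorithm.

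The other inputs are spread through the article:

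- Centres (Abstract, Methods): "This multicentre randomized clinical trial will take place in 6 Dutch hospitals".
- Gender (Administrative information): "Sexes eligible for study: both".
- Pain location: the levels are not listed. The entry criterion reads "LBP and/or leg pain intensity should be 5 or higher measured with the 11-box NRS 0-10", which suggests either two levels (back, leg) or three (back, leg, both).
- PCS at entry (Patient population): "patients must show at least a moderate level of pain catastrophizing (PCS ≥ 20"), so 35 is an eligible score.
- Size (Sample size calculation): "this is rounded to 94 patients in order to ensure even group size of 47 patients per group".

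The section on primary study parameters compares mean PCS at 6 months between groups, using a one-sided 95% confidence interval and a margin of 7 points. It mentions no adjustment for baseline PCS or for any stratification factor.

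**The concern.** There are two separate matters here.

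The first is an error in an operative rule. The bands share the value 35, so two centres can place the same score in different strata. PCS is both the entry measure and the primary outcome, so it is the stratification factor on which clarity matters most. The wording *per group* is also faulty, because group is what is being allocated and cannot define a stratum.

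The second is conditional. Four factors crossed over 94 patients leave about one or two patients per cell. If allocation uses permuted blocks inside each cell, most blocks never fill, and an unfilled block does not force balance. The trial would then lose much of the PCS balance that stratification is meant to give. A chance imbalance in baseline PCS would pass into an unadjusted comparison of 6-month means, which is the comparison set against the 7-point margin.

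**Working it through.** **1. The plan's own sample size.** Inputs from Sample size calculation: margin 7, SD 12.04, power 80%, 5% significance taken as one-sided to match the one-sided 95% interval, true difference 0.

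n per group = 2 × [12.04 × (1.645 + 0.842) / 7]² = 36.58, rounded up to 37. Total 74. With 20% dropout, 74 / 0.80 = 92.5, and the next even total is 94. The plan's figures are reproduced.

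**2. The overlap.** Bands are 20-35 and 35-52. The score 35 is in both. It is one of 52 − 20 + 1 = 33 possible whole-number scores. No assumption is needed.

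**3. Number of cells, if fully crossed.**

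- Two pain locations: 6 × 2 × 2 × 2 = 48 cells; 94 / 48 = 1.96 patients per cell.
- Three pain locations: 6 × 2 × 2 × 3 = 72 cells; 94 / 72 = 1.31 patients per cell.
- Centre and PCS only: 6 × 2 = 12 cells; 94 / 12 = 7.8 patients per cell.

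Distributing 94 patients at random over 48 to 72 cells, with equal or assumed unequal cell sizes, leaves 42 to 68% of cells with at most one patient and 83 to 96% with fewer than four.

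**4. Balance under within-cell blocking.** Simulation of 94 patients with permuted blocks of 4 in every cell (assumed), equal or uneven centre sizes (assumed), and the other factors split evenly (assumed). Ranges cover repeated runs under these variants.

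| Quantity | 48 cells | 72 cells | 12 cells | Simple randomisation |
|---|---|---|---|---|
| SD of arm-size difference (patients) | 6.0-6.6 | 7.0-7.5 | 3.1-3.2 | 9.7 |
| Arm-size difference of 10 or more | 14-17% | 20-23% | about 0.5% or less | 35% |
| Arm difference of 8 or more within one PCS band | 7-10% | 12-16% | 0.1-0.2% or less | 27% |
| Exactly 47:47 | 10-13% | 10-13% | about 25% | 8% |

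The SD for simple randomisation is √94 = 9.7.

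The arms can also be compared on the proportion of patients in the high PCS band. The SD of that difference is about 6.4 to 8.1 percentage points with 48 to 72 cells, about 3.4 with 12 cells, and about 10 with simple randomisation. A difference above 15 points occurs in about 2 to 6% of trials with 48 to 72 cells, in almost none with 12, and in 14 to 15% with simple randomisation.

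**5. What that does to the primary comparison.** The shift in the unadjusted difference equals the difference in high-band proportion times the difference in mean 6-month PCS between bands. The article does not give the second quantity. With a 15-point imbalance, a shift of 1 PCS point needs the bands to differ by 1 / 0.15 = 6.7 points at 6 months.

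**6. Effect on power.** After 20% dropout, standard error = 12.04 × √(1/(0.8a) + 1/(0.8b)) and power = Φ(7 / SE − 1.645).

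- 47:47: SE 2.777, power 80.9%
- 52:42: SE 2.793, power 80.6%
- 54:40: SE 2.808, power 80.2%
- 57:37: SE 2.842, power 79.3%

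**The case against.** The strongest reply is that everything beyond the overlap rests on facts the article does not state. Blocks are nowhere mentioned, the levels of pain location are not given, and a condensed article commonly leaves the allocation algorithm to the full protocol. Under minimisation the cell-count argument largely disappears. This stands, which is why that part is put conditionally.

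Second, stratification over 48 to 72 cells is still better than simple randomisation on every row of the table, and arm-size imbalance costs almost no power. Both stand. It would be wrong to say that the scheme secures nothing.

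Third, the overlap affects one score in 33. With equal allocation, placing that patient in either band does not bias the comparison. The article has patients complete the PCS electronically in the same software that randomises, so the band may be derived automatically. That limits the harm, but software also needs a rule for 35 and the stated rule gives none.

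Fourth, adjustment for baseline may be set out in an analysis plan that is not shown, and elsewhere the article calls the primary outcome a change on the PCS. Both are possible. The section that fixes the primary comparison describes only a difference in mean scores at 6 months.

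A reader might go further and infer that the plan promised a 47:47 split and fails to deliver it. The document does not support that. The figure of 47 per group explains why 92.5 was rounded up to 94 and is a planning size. The overlap at 35 does not unbalance the arms. Even 12 cells give exactly 47:47 in only about a quarter of trials, so an exact split is not a fair test of the scheme.

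**Conclusion.** The concern holds in two parts of different strength.

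Certain, and free of assumptions: the PCS bands overlap at 35, so an eligible patient with that score has no unique stratum, and *per group* cannot be a stratification factor. This is a small error in a rule that staff must apply.

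Conditional on full crossing, two or three pain locations, and permuted blocks of 4 within cells: 48 to 72 cells are too many for 94 patients. The SD of the arm-size difference is about twice that obtained with centre and PCS alone (6 to 7.5 against about 3). A within-band arm difference of 8 or more rises from 0.1-0.2% or less to roughly 7-16%. The loss of power at 54:40 is 80.9 − 80.2 = 0.7 points and is not a reason to act. The reason to act is PCS balance, given a primary comparison described without adjustment.

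**What to change.** Regardless of the allocation method:

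- Make the PCS bands disjoint, for example 20-34 and 35-52, and have the software derive the band from the entered score.
- Delete *per group* from the sentence on stratification.
- Adjust the primary PCS comparison for the stratification factors: baseline PCS as a score, gender, pain location, and centre where feasible. Keep the 7-point margin and the one-sided 95% interval.

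Only if permuted blocks within fully crossed cells are in use: for patients still to be randomised, stratify by centre and PCS only (12 cells), or use minimisation with a random element over all four factors. If minimisation is already in use, say so, and no change of scheme is needed.

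Cost: a short amendment and, if the scheme changes, reconfiguration of the randomisation module. Patients already randomised keep their allocation. With 12 cells, gender and pain location are handled by the analysis model and no longer by separate strata.

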### Statistical analysis

All main analyses will be performed according to the intention-to-treat principle. Hence, all patients who do not show sufficient pain reduction in the first phase will still be considered for the analyses. In addition, an exploratory per protocol analysis will be performed on those that do show sufficient benefit in the first phase.

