### Primary study parameters

Between-group differences in mean PCS scores at 6 months will be computed including the one-sided 95% confidence interval. The upper bound of the difference will be compared to the non-inferiority margin of 7 points. If the margin lies in the 95% confidence interval, the null-hypothesis that active recharge is not inferior to passive recharge cannot be rejected.

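### Patients can leave burst stimulation before the 6-month PCS, but the only analysis set besides ITT is defined by first-phase benefit and not by waveform received

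*Protocol article*

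**What the plan says.** The Background section sets the objective as a comparison of passive with active recharge burst stimulation, with the PCS at 6 months as primary outcome. The Sample size calculation section says: "This study follows a non-inferiority setup based on the primary outcome measure, the PCS". The Primary study parameters section says: "Between-group differences in mean PCS scores at 6 months will be computed including the one-sided 95% confidence interval". The upper bound is then compared with 7 points.

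The Study procedure section gives two routes away from burst before 6 months:

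- **Test phase.** If pain reduction is below 50% after two weeks, the test is extended by a week and "other (non-burst) waveforms possible with the implanted system can be tried, with the aim to induce pain relief". Those who then reach 50% stay in the study and are followed up.
- **Any later time.** If, in any trial phase, "patients encounter decreased efficacy or insufficient pain relief, they may enter the open label phase prematurely". Non-burst waveforms are permitted there. Table 1 agrees: it allows the open-label phase on loss of effect from implantation through 6 months.

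The Statistical analysis section makes ITT the basis of all main analyses and adds only that "an exploratory per protocol analysis will be performed on those that do show sufficient benefit in the first phase".

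**The concern.** The question is about recharge pattern, but the 6-month PCS of a patient who has moved to another waveform no longer reflects the recharge pattern to which that patient was randomised. Switching is triggered by poor relief. A worse burst waveform would therefore tend to send more of its patients to other stimulation, and the ITT contrast would tend to shrink. In a superiority trial that costs power. In a non-inferiority trial it makes the claim easier to reach.

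A per-protocol analysis is the usual check on this, but the stated set cannot provide it. Membership depends on early response and not on what was delivered up to month 6. A patient who responds in the test phase and leaves burst at month 2 stays in. A patient who reached 50% relief only on a non-burst waveform in the added week may also stay in, depending on whether the first phase is read to include that week. At stake is whether a positive result could be read as a statement about the two burst waveforms, or only about starting treatment with one system or the other.

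**Working it through.** **Inputs from the Sample size calculation and Primary study parameters sections:** margin 7 points, SD 12.04, "80% power and 5% significance level", one-sided 95% interval, 37 per group, 47 per group after inflation.

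**Step 1: reproduce the sample size.** With a true difference of 0,

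n per group = 2 × 12.04² × (1.645 + 0.842)² / 7² = 36.6, so 37 per group and 74 in total. Then 74 / 0.80 = 92.5, rounded to 94. The figure reproduces. The 20% covers drop-out and failed initial trials, and nothing allows for switching.

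**Step 2: effect of switching on ITT.** Assumptions, none of them in the documents: the true difference while on burst equals the margin (7), a share s of each arm has switched by month 6, and switchers show no difference between arms.

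- ITT difference = 7(1 − s)
- SE = 12.04 × √(2/n): 2.799 at 37 per group, 2.484 at 47
- Probability of declaring non-inferiority = Φ(7s/SE − 1.645)

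| s | ITT difference | n = 37 | n = 47 |
|---|---|---|---|
| 0 | 7.0 | 5.0% | 5.0% |
| 10% | 6.3 | 8.2% | 8.6% |
| 20% | 5.6 | 12.6% | 14.0% |
| 30% | 4.9 | 18.6% | 21.2% |
| 40% | 4.2 | 26.0% | 30.2% |

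Calculations from the t distribution agree to within about 0.3 points. Put the other way, at 20% switching the difference between the burst waveforms would have to be 7 / 0.8 = 8.75 points before the ITT difference reached the margin.

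**Step 3: relax the equal-outcome assumption.** If switchers keep a gap g, the ITT difference is 7(1 − s) + g·s. At s = 20% and n = 37:

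- g = 0: 5.6, error 12.6%
- g = 3.5: 5.6 + 0.7 = 6.3, error 8.2%
- g = 7: 7.0, error 5.0%

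**Step 4: cost of an on-waveform set.** If 30 per group remain on burst, SE = 12.04 × √(2/30) = 3.109, and power at a true difference of 0 is Φ(7/3.109 − 1.645) = 73%. At 37 per group it is 80%.

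**Step 5: selection in an on-waveform set.** Staying on burst is itself a response. In a simulation with a true difference of 7, 37 per arm before exclusions and 20% switching overall for poor relief, false non-inferiority in the still-on-burst set was about 6%, 8% and 13% when the assumed correlation between relief and PCS was 0.3, 0.5 and 0.7. It exceeded 30% at a correlation of 1. Such a set is therefore not unbiased either.

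**The case against.** Five objections deserve an answer.

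**ITT is a legitimate choice.** It answers which system and burst strategy to start with under ordinary care, and the protocol deliberately keeps poor first-phase responders. This stands, and ITT should remain primary. It does not by itself support a statement about recharge pattern, which is the stated objective.

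**The direction is not certain.** A reader might infer that switching must favour non-inferiority. The documents do not support that. Switchers can use only what their implanted system offers, and the two arms have different manufacturers' systems, so the alternatives may differ and add a difference of their own. The trigger is pain relief while the endpoint is the PCS, so rescue of the PCS is a further assumption. Equal switching in both arms is also a simplification if one waveform is truly worse. Dilution is the expected direction, no more.

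**The stated set may already exclude test-phase switchers.** A reader might infer that no analysis comes near a burst-versus-burst comparison. The natural reading of first-phase benefit is success during the two-week burst test, which would leave out those who switched in the added week. The wording does not settle it. The gap that remains on either reading is patients who leave burst after implantation.

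**An on-waveform set also selects on response.** This is correct, as Step 5 shows. It rules out using that set as a replacement for ITT, and it makes a mandatory co-primary rule debatable. It does not defend the current set, which selects on response and does not remove later switchers.

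**Detail may sit in the SAP or full protocol.** Counts of switches and similar reporting may well be there. The point here concerns sets that the article itself fixes.

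**Conclusion.** The point holds in a limited form. Switching away from burst before the primary endpoint is permitted, ITT is the only main analysis of a non-inferiority test, and the exploratory per-protocol set as worded does not exclude patients who leave burst after implantation. No stated analysis would therefore show whether a non-inferiority finding had been helped by other waveforms.

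The size is unknown, because no switch rate is given. The range of about 8% to 26% at 37 per group rests on an assumed 10% to 40% switching, equal in both arms, a true difference of 7 and no gap among switchers. It falls back towards 5% as switchers retain the gap. It would be wrong to conclude that the trial's error rate is inflated by a known amount, or that the ITT analysis is invalid. What the documents support is that the supporting set is defined on the wrong variable for the question asked.

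**What to change.** - Keep ITT as the primary analysis.
- Redefine the per-protocol set as patients who stayed on their randomised burst waveform up to the 6-month PCS, with no non-burst switch (including in the added test week) and no premature entry to the open-label phase.
- Prespecify it as a key supporting analysis, with the same one-sided 95% interval and 7-point margin.
- Conclude non-inferiority of the recharge waveforms, as distinct from the strategy of starting with one system, only if both analyses agree.
- Record the waveform in use at each visit, and report the number and timing of switches by arm.
- State in the plan that staying on burst depends on response, so the set complements ITT and does not give an unbiased waveform comparison.

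The cost is analysis wording and one data field per visit; stimulation charge is already collected at follow-up contacts. Power is lower in the smaller set, about 73% if 30 per group remain on burst, and residual selection cannot be removed. The clinical rules on switching are left as they are.
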